**Figure 2 figure2:**
[figure not shown]
CARE intervention components.

#### Control Group

The control group will receive usual care, which in the context of melanoma care at the Juravinski Cancer Centre includes no form of rehabilitation. Participants assigned to this group will not receive a rehabilitation referral from the study team; however, they are not limited from discussing rehabilitation options with their medical oncologist if they wish to learn more. Participants are not restricted from accessing rehabilitation services outside of the study.

### Outcomes and Measurement Instruments

Outcomes will be assessed before and after the intervention by a trained assessor blinded to group allocation and will be documented on REDCap (Vanderbilt University; a secure online research application for managing research data). Assessments will be scheduled to coincide with participants’ cancer center appointments to improve accessibility for all patients.

#### Primary Outcome: Feasibility (Research Question 1)

##### Overview

The primary outcome of this pilot trial will be feasibility of the intervention. Feasibility will be measured by recruitment, retention, adherence rates, and participant satisfaction. Recommendations for progression to a full-scale trial will be based on feasibility data and published recommendations for progression criteria [26-28]. Table 2 outlines feasibility components and interpretation or progression criteria.

**Table 2 table2:** Feasibility components and progression criteria [26,28].

Feasibility criteria	Go: proceed to RCT^a^	Amend: proceed with changes	Stop: do not proceed unless changes are possible
Patient recruitment	If >70% of eligible potential participants are recruited to take part	If 50% to 70% of eligible potential participants are recruited to take part	If <50% of eligible potential participants are recruited to take part
Participant retention	If >70% of enrolled participants are retained until study completion	If 50% to 70% of enrolled participants are retained until study completion	If <50% of enrolled participants are retained until study completion
Participant adherence	If participants attend >70% of intervention sessions	If participants attend 50% to 70% of intervention sessions	If participants attend <50% of intervention sessions
Participant satisfaction	If each of the 4 AIM^b^ questions has a median response score of ≥4 out of 5	If each of the 4 AIM questions has a median response score of 3 out of 5	If each of the 4 AIM questions has a median response score of ≤2 out of 5

^a^RCT: randomized controlled trial.

^b^AIM: Acceptability of Intervention Measure.

##### Recruitment Rate

Recruitment rate for this study is defined as the percentage of eligible patients referred to the study who agree to participate.

##### Retention Rate

Retention rate is the percentage of recruited and enrolled participants who are retained until study completion.

##### Adherence Rate

Adherence rate will be measured as adherence to the intervention session and is defined as the number of sessions attended.

##### Participant Satisfaction

Participant satisfaction will be measured using the Acceptability of Intervention Measure [29]. This measure assesses 4 components of satisfaction on a 5-point Likert scale ranging from 1 (completely disagree) to 5 (completely agree) [29]. Higher scores represent higher levels of intervention acceptability and satisfaction [29].

#### Secondary Outcomes (Research Question 2)

Secondary outcomes to be assessed include an overall impairment score, physical activity level, functional mobility, ROM, grip strength, quality of life, perception of health status, and medication use.

#### Overall Impairment Score

The Edmonton Symptom Assessment Scale (ESAS) [30] will be used to measure overall impairment. The ESAS is a self-report measure designed to assess the severity of various symptoms commonly experienced by those with cancer [30]. It consists of 8 symptoms (pain, fatigue, drowsiness, nausea, appetite, shortness of breath, depression, and anxiety), which are each rated on a scale of 0 (no symptoms) to 10 (worst possible symptoms), along with a question on overall well-being at a single point in time (rated from 0 [best well-being] to 10 [worst possible well-being]) [30]. Higher scores indicate more severe symptoms and higher overall symptom burden [30]. The ESAS has good reliability and validity among survivors of cancer [31].

#### Physical Activity Level

The Godin Leisure Time Exercise Questionnaire [32] will be used to assess physical activity level. It is a self-report tool designed to assess an individual’s level of physical activity over a 7-day period [33]. Respondents report the frequency of mild, moderate, and vigorous physical activity they engage in for at least 15 minutes during a typical week. Higher scores indicate a greater level of physical activity [33]. A score of 24 or more indicates “sufficiently active” or meeting current exercise guidelines, while lower scores suggest “insufficient activity” [32,33]. This measure has demonstrated high levels of reliability and validity in survivors of cancer [34].

#### Functional Mobility

Functional ability will be assessed using the 30-second sit-to-stand (30sSTS) test [35] and the 6-minute walk test (6MWT) [36]. Standardized instructions will be provided by the assessor before each test, and participants will receive assessor supervision and support throughout administration of these tests. The 30sSTS is a simple assessment of functional ability in which participants begin by sitting in a chair with their arms crossed over their chest. Participants rise to a standing position and then return to a seated position, repeating the movement as many times as possible within 30 seconds. The number of completed repetitions is counted as the score, with higher scores representing higher levels of functional mobility. Normative values exist by age and sex [37]. Reliability and validity studies have shown this test to be reliable and valid when assessing physical performance in survivors of cancer [38]. The 6MWT has the participant walk as far as possible in 6 minutes along a flat, straight corridor. Participants are encouraged to walk at a comfortable pace and can pause or use an assistive device if necessary. Outcomes are interpreted as the total distanced walked (meters) in 6 minutes. Normative values exist based on age and sex [39]. The 6MWT has demonstrated high reliability and validity in survivors of cancer [40].

#### ROM

ROM will be assessed using goniometry. Goniometry is the gold standard for ROM measurement [41]. Based on the location of the participants’ melanoma surgery and lymph node dissection (ie, neck, axillary, or groin), ROM assessments will be conducted for the upper extremities (UEs; if neck or axillary surgery) or lower extremities (LEs; if groin surgery). For UE ROM, movements to be assessed include shoulder flexion, abduction, internal rotation, and external rotation; elbow flexion and extension; and wrist flexion, extension, radial deviation, and ulnar deviation. For LE ROM, movements to be assessed include hip flexion, extension, internal rotation, and external rotation; knee flexion and extension; and ankle plantar flexion and dorsiflexion. Normative values exist for each joint, with higher values representing better ROM [41].

#### Grip Strength

Handheld dynamometry [42] will be used to measure grip strength. For this test, individuals will sit in a comfortable position with their elbow flexed at 90° and their wrist in a neutral position while exerting maximal force by squeezing the handheld device. The test will be repeated twice for each hand, and the average grip strength will be calculated and recorded in kilograms. Normative values exist for age and sex, and higher scores indicate greater muscle strength [42]. Handheld dynamometry exhibits good reliability and validity in survivors of cancer [43].

#### Quality of Life

The Functional Assessment of Cancer Therapy-Melanoma (FACT-M) [44] will be used to assess quality of life. This self-report measure includes a series of items that evaluate various domains of health-related quality of life, including physical well-being, social or family well-being, emotional well-being, functional well-being, and melanoma-specific concerns. Each item is rated on a Likert scale ranging from “not at all” to “very much.” Outcomes can be interpreted based on both subscale and total score, with higher scores indicating better quality of life. Reliability and validity studies support the FACT-M’s use among those with cancer [45].

#### Perception of Health Status

The EQ-5D-3L [46] will be used to measure health status. It encompasses 5 dimensions: mobility, self-care, usual activities, pain, and anxiety or depression; respondents rate the severity of each dimension as having no problems, some problems, or extreme problems. It also includes a visual analog scale where respondents will rate their overall health on a scale of 0 (worst imaginable health) to 100 (best imaginable health). Higher scores indicate better health status. Research has demonstrated its reliability and validity among survivors of cancer [46].

#### Medication Use

Medication use will be collected using a self-report questionnaire. The questionnaire will ask participants to list the medications they are currently using and have used 7 days prior to the assessment (drug name and dosage). After the surgery, the questionnaire will also ask if they have taken specific medication since surgery (acetaminophen, antiinflammatories, muscle relaxants, neuropathic pain medications, or narcotics), how long they took the medication after the surgery, and the dosage. Tracking medication will allow us to identify changes in medications that may occur during the perioperative period, explore whether medication use acts as a potential confounder when interpreting intervention-related change, and inform the design and covariate selection for a future larger-scale trial.

#### Adverse Events (Research Question 3)

The safety of our intervention will be assessed by monitoring adverse events throughout the study period. Participants will be asked to report any adverse event at each study contact. They will be classified by type, severity, duration, and relatedness to the intervention based on the National Cancer Institute Common Terminology Criteria for Adverse Events [47]. Serious adverse events will be reported to the Hamilton Integrated Research Ethics Board in accordance with institutional policies. The trial will be suspended if one or more serious adverse events are deemed definitely or probably related to the intervention by the study team and research ethics board.

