### Research Questions and Hypotheses

This trial will answer 3 research questions.

First, is perioperative rehabilitation feasible for individuals diagnosed with melanoma requiring neoadjuvant immunotherapy and then receiving surgery? We hypothesize that the intervention will be feasible, as demonstrated by recruitment, retention, and adherence rates of >70% and high patient satisfaction with the intervention.

Second, do individuals with melanoma who participate in perioperative rehabilitation have improved outcomes (improved overall impairment score, physical activity level, functional mobility, ROM, grip strength, quality of life, perception of health status, and medication use) compared to those receiving usual care (no rehabilitation)? We hypothesize that those participating in the intervention will have improved overall impairment score, physical activity level, functional mobility, ROM, grip strength, quality of life, perception of health status, and medication use, compared to those receiving usual care.

Third, what is the frequency and nature of adverse events associated with perioperative rehabilitation for individuals with melanoma? We hypothesize that perioperative rehabilitation for individuals with melanoma will be safe and associated with few, if any, intervention-related adverse events.

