## Methods

### Study Design

This is a pilot, parallel group randomized controlled trial (RCT). It will use a 1:1 allocation ratio, and participants will be randomly assigned to either the intervention or control group. Outcome assessments will be conducted at baseline and postintervention time points with assessors and data analysts blinded to group allocation. The protocol adheres to the SPIRIT (Standard Protocol Items: Recommendations for Interventional Trials) 2025 checklist [21] for protocols of randomized trials. Figure 1 shows the flow of participants across the study and associated analysis time points.

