#### Intervention Group

The intervention group (CARE intervention) will include 4 perioperative intervention sessions led by a physiotherapist or kinesiologist trained in the treatment of individuals with cancer. The total intervention time will be approximately 4 months, with 2 of the intervention sessions occurring prior to surgery and 2 occurring after surgery. The intervention was designed to coincide with the immunotherapy treatment regime and key perioperative milestones [20]. The 2 preoperative sessions provide an opportunity for assessment, exercise education, prehabilitation, and development or an individualized exercise plan. They will be conducted in person whenever participants visit the cancer center for a scheduled appointment. The postoperative sessions support reassessment, progression of rehabilitation, management or postsurgical issues, and transition to long-term self-management. Participants will have the option of taking part in the postsurgery sessions in person or virtually. The approximately 4-month duration was selected to encompass the presurgical and early postsurgical recovery period while maintaining feasibility and minimizing participant burden in this pilot trial.

Each intervention session will include five components based on our previous research and guidelines for survivors of cancer: (1) review of current symptoms and function, (2) educational modules on exercise viewed on an iPad with the trainer, (3) tailored rehabilitation to maximize function, (4) home exercise program development or review, and (5) action plan development for participants to work on between sessions. Table 1 describes each intervention component. Figure 2 provides an overview of the CARE intervention components across the study period.

**Table 1 table1:** Components of the CARE intervention.

Component	Description
Review of current symptoms and function	Sessions 1-4 (items checked) Current symptoms (eg, pain, fatigue, range of motion, strength, balance scan) Posture Functional concerns (mobility observation) Vital signs (eg, heart rate, blood pressure, SpO2) Other changes since last visit

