### Data Analysis Plan

Feasibility outcomes (research question 1; recruitment, retention, adherence, and satisfaction rates) will be analyzed using descriptive statistics (mean [SD] or frequency [%]), as appropriate. Preliminary estimates of effects *(*research question 2*)* will be reported using mean (SDs) and CIs of outcomes for continuous outcomes. Given the pilot nature of this trial and the limited sample size, Cohen *d* effect sizes will be calculated and reported for each secondary outcome. Effect sizes will be interpreted alongside CIs to provide estimates of the magnitude of effect and to inform a future full-scale trial. Medication use will be summarized descriptively for each treatment group. The proportion of participants using each medication class will be reporting using frequencies (%s), while duration of medication use and dosage will be summarized using mean (SDs) or median (IQRs), as appropriate. The frequency and nature of adverse events (research question 3) will be summarized descriptively. An intention-to-treat analysis will be conducted, with missing data handled using multiple imputation. STATA/MP (version 14; StrataCorp) will be used for all statistical analyses, with significance set at *P*<.05.

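### Adverse events are asked about at every study contact, which on the described schedule means five contacts after allocation in the intervention arm and one in control, so all-cause event frequencies set out by arm would not be comparable

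*Protocol article*

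**What the plan says.** The section Adverse Events (Research Question 3) sets the aim, "The safety of our intervention will be assessed by monitoring adverse events throughout the study period", and the collection rule, "Participants will be asked to report any adverse event at each study contact". The rule covers every participant and any event. Events are then classified by type, severity, duration and relatedness to the intervention.

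The contacts that the article describes are:

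- **Both arms** (Study Design): "Outcome assessments will be conducted at baseline and postintervention time points with assessors and data analysts blinded to group allocation". Under Procedure, the baseline assessment comes before participants are divided into groups.
- **Intervention arm** (Intervention Group): "The intervention group (CARE intervention) will include 4 perioperative intervention sessions led by a physiotherapist or kinesiologist", two before surgery and two after. Table 1 has each session review symptoms, function, vital signs and other changes since the last visit.
- **Control arm** (Control Group section): "The control group will receive usual care, which in the context of melanoma care at the Juravinski Cancer Centre includes no form of rehabilitation". No interim study contact is described.

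Under Research Questions and Hypotheses, the safety hypothesis is that perioperative rehabilitation "will be safe and associated with few, if any, intervention-related adverse events". The Data Analysis Plan says: "The frequency and nature of adverse events (research question 3) will be summarized descriptively". It does not say whether that summary is by arm, and it attaches no interval to it.

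**The concern.** How often events are recorded depends on how often people are asked and how far back they must remember. Here both differ by arm. Intervention participants are asked repeatedly, at sessions that already go through their symptoms, by the person delivering the intervention. Control participants are asked once after allocation, by a blinded assessor, about a period of some 4 months. A control participant who leaves before follow-up has no described occasion after allocation on which to report anything, whereas an intervention participant who leaves has been asked at each session attended. The Sample Size section allows for dropout of up to 30%.

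Background events are likely to be common. Everyone receives immunotherapy and surgery, and the Background section names fatigue, reduced muscle strength and impaired physical function as possible consequences. Such events can resemble exercise-related ones. A report of a two-arm randomized trial may well show event counts in two columns, and a reader would take any difference as informative. With this collection rule, part or all of the difference could come from unequal questioning.

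A second, smaller issue concerns the hypothesis of safety. Few or no related events among about 15 people is weak evidence unless an upper limit is shown beside it.

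**Working it through.** The article gives no contact count, event rate or recall assumption, so there is no figure of the plan to reproduce on this point. The count below is built from the described schedule.

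**Step 1. Contacts after allocation.** Baseline precedes allocation and cannot capture events that arise afterwards, so it is left out.

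| | Sessions | Follow-up assessment | Total |
|---|---|---|---|
| Intervention | 4 | 1 | 5 |
| Control | 0 | 1 | 1 |

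Full attendance is assumed. The Sample Size section plans on a proportion of 0.75, based on expected adherence. Applied to sessions, that gives 4 × 0.75 = 3 attended on average, and so 3 + 1 = 4 occasions against 1.

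**Step 2. What this could do to recorded frequencies.** This is an illustration on assumptions that are not in the document: equal true event rates in both arms, contacts evenly spaced over 120 days, and a chance of reporting an event that decays exponentially with time since it happened. For a recall half-life h, put k = ln 2 / h. The share of events reported over a recall window of L days is f(L) = (1 − e^(−kL)) / (kL). The window is 120 / 5 = 24 days in the intervention arm and 120 days in control.

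| Half-life h (days) | f(24), intervention | f(120), control | Apparent ratio |
|---|---|---|---|
| 14 | 0.59 | 0.17 | 3.5 |
| 30 | 0.77 | 0.34 | 2.3 |
| 60 | 0.87 | 0.54 | 1.6 |
| 120 | 0.93 | 0.72 | 1.3 |

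A cruder assumption that simply fixes the capture shares gives 0.8 / 0.5 = 1.6, or 0.7 / 0.6 = 1.17. In every case the true ratio is 1.0. The direction is stable, but the size depends wholly on the assumption.

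**Step 3. What zero related events would show.** With 0 events in n = 15 intervention participants, the exact (Clopper-Pearson) two-sided 95% upper limit is 1 − 0.025^(1/15) = 0.218. The one-sided 95% limit is 1 − 0.05^(1/15) = 0.181. A clean record in the whole intervention arm is therefore compatible with about 22% of participants having a related event.

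**The case against.** The strongest reply is that the plan never proposes to compare event frequencies between arms. Research question 2 names usual care as its comparator; research question 3 does not. The Data Analysis Plan summarizes medication use for each treatment group but says only that adverse events will be described. The stated route to attribution is a case-by-case judgement of relatedness. Related events can arise only in the intervention arm, which is the arm asked most often, so close questioning there helps the question actually posed. If the arms were compared all the same, the likely error would make the intervention look less safe, which works against the hypothesis. All of this stands.

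A reader might therefore be tempted to conclude that the safety question itself is answered with built-in bias. The document does not support that, because the bias attaches to an arm comparison that the plan does not state. A reader might also count the schedule as six contacts against two. That includes the baseline assessment, which comes before allocation and so does not bear on events after it.

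It is also fair that the article does not define a study contact, that its two figures are not shown here, and that interim control contacts are undescribed rather than excluded. If the full protocol schedules equal contacts for controls, the imbalance goes. The interval for related events could likewise be left to an analysis plan.

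One part of the concern survives these replies. The rule collects any event from both randomized arms, it acts at data collection, and the article gives no caution about setting the results side by side. Control events that were never asked about cannot be recovered at analysis.

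**Conclusion.** The point holds in a limited form. On the described schedule, adverse events are sought on 5 occasions after allocation in the intervention arm and on 1 in control. All-cause frequencies by arm would not be comparable and would tend to show a spurious excess in the intervention arm. The direction rests on the described schedule being complete and on recall fading over months. The size cannot be derived from the document, and the ratios of 1.3 to 3.5 are illustration only. The relatedness-based answer to research question 3 is not invalidated. That answer does need an upper limit: with no related events among 15 participants, a rate of up to about 22% remains compatible with the data, so an unqualified statement of safety would claim too much. For a descriptive pilot this should be changed because the remedy is cheap, but it does not undermine the trial.

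**What to change.** 1. At the existing follow-up assessment, give both arms the same structured adverse-event checklist with the same recall period. Use only that source for any frequencies shown by arm.
2. Report events raised at sessions separately, labelled as intervention-arm-only data, for the relatedness-based answer to research question 3. Leave ongoing safety monitoring and reporting as they are.
3. Report the proportion of intervention participants with a related event with an exact 95% confidence interval, and word the conclusion on safety to its upper limit.

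The cost is one short form at a visit that already takes place and a sentence or two in the analysis plan. The Results section reports 3 participants recruited so far and Table 3 starts follow-up assessments in October 2026, so on that timeline a prompt change could precede the first of them.

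The downside is that a single long recall will miss minor events in both arms. Earlier questioning at sessions may also still prompt recall in the intervention arm, so the checklist reduces the imbalance without removing it. The by-arm comparison should remain descriptive and carry that caution.
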